## Abstract

**Background:**

This randomized, parallel-group study aims to investigate the effects of the probiotic *Bifidobacterium bifidum* G9-1 (BBG9-1) on the symptoms of diarrhea or constipation in patients with type 2 diabetes mellitus (T2DM).

**Methods:**

This study will examine 100 patients with T2DM who suffering from symptoms of diarrhea or constipation. Eligible patients will be randomly assigned 1:1 to two groups (group A, BBG9-1 group; group B, control group), after the baseline examination. Patients assigned to group A will receive probiotic BBG9-1 oral administration along with their current treatment for 12 weeks, and patients assigned to group B will continue the current treatment for 12 weeks without probiotic BBG9-1 oral administration. Subsequently, examinations similar to the baseline examinations will be performed. The primary endpoint will be a change in the Gastrointestinal Symptom Rating Scale (GSRS) total score from baseline to week 12. Secondary endpoints will include the following: change and percent change in parameters such as GSRS subdomain scores, fecal properties/Bristol stool form scale, defecation frequency, biomarkers, gut microbiota, and macronutrients and factors that affect GSRS total score or constipation/diarrhea subdomain scores from baseline to week 12.

**Discussion:**

The results of this study will clarify the utility of probiotic BBG9-1 in the treatment of diarrhea or constipation in patients with T2DM.

**Trial registration:**

jRCTs051220127.

## Introduction

### Background and rationale

The number of patients with type 2 diabetes mellitus (T2DM) is increasing worldwide [1]. In addition to microvascular and macrovascular complications, well-known complications of diabetes [1] and gastrointestinal diseases, such as reflux esophagitis, diarrhea, and constipation, have been reported to be associated with diabetes [2–4]. Diabetes medications reportedly increase the risk of gastrointestinal complications, such as constipation and diarrhea [5,6].

Recent studies have clarified the association between the gut microbiota and T2DM [7–11]. Dysbiosis causes a decrease in short-chain fatty acids and branched-chain amino acids, leading to chronic inflammation and insulin resistance [9]. On the other hand, it has been reported that probiotic bifidobacteria improves dysbiosis. Symptoms of diarrhea and constipation in individuals without diabetes have been improved by probiotic bifidobacteria [12–14]. In addition, we recently revealed that the probiotic *Bifidobacterium bifidum* G9-1 (BBG9-1) improved the symptoms of constipation and diarrhea in patients with T2DM [15]. However, the study was an open-label, single-arm exploratory study [15], and further research is needed to determine its effectiveness and mechanism. Therefore, this randomized, parallel-group study will investigate the efficacy of the probiotic BBG9-1 on the symptoms of diarrhea or constipation in patients with T2DM.

### Objectives

The purpose of this study was to evaluate the efficacy of probiotic BBG9-1 on the symptoms of diarrhoea or constipation in patients with T2DM using randomized, parallel-group study with a control group.

### Trial design

Open-label, randomized, multicenter, parallel-group study

## Materials and methods: Participants, interventions, and outcomes

### Study setting

This open-label, randomized controlled trial (Efficacy of **B**ifidobacteria **in**take on g**a**st**r**ointestinal s**y**mptoms in **S**ymptomatic **T**ype 2 diabetes mellitus patients in **A**bdominis: an open-label, **R**andomized controlled trial [**Binary STAR** study]) will be performed for 12 weeks in Japanese outpatients with T2DM at the Hospital of the Kyoto Prefectural University of Medicine (Kyoto, Japan), Matsushita Memorial Hospital (Moriguchi, Japan), and Kameoka Municipal Hospital (Kameoka, Japan). A total of 100 patients with T2DM, who have symptoms of diarrhea or constipation, will be included. This study was registered with the Japan Registry of Clinical Trials (jRCTs051220127) and approved by the ethics committees of the Kyoto Prefectural University of Medicine (CRB 2021028). This study will be conducted in accordance with the principles of the Declaration of Helsinki.

### Eligibility criteria

Patients must satisfy all of the following inclusion criteria. The inclusion criteria are as follows: (1) symptoms of diarrhea or constipation; (2) three or higher in Gastrointestinal Symptom Rating Scale (GSRS) subdomain score (diarrhea or constipation); (3) T2DM patients without diabetic polyneuropathy; (4) no new antibiotic usage within 12 weeks prior to consent; (5) no new diet interventions within 12 weeks prior to consent; (6) no changes in medications which can affect gastrointestinal symptoms and microbiome (addition or discontinuation of medications or change in use or dosage of medications) within 12 weeks prior to consent; (7) aged 20 and up and under 75 years or less at the time of consent; (8) written consent obtained from the individual. The exclusion criteria are as follows: patients with (1) mean defecation frequency < 1 or > 42 times/ week within 4 weeks before giving their consent; (2) structural diseases, including inflammatory diseases (infectious enteritis, diverticulitis, Crohn’s disease, and ulcerative colitis), and stenotic lesions, diagnosed by colonoscopy within 5 years before giving their consent; (3) having both ≥ 3 on the GSRS constipation subscale and > 4 on the Bristol stool scale; (4) having both ≥ 3 on the GSRS diarrhea subscale and < 4 on the Bristol stool scale; (5) gastrointestinal symptoms of both diarrhea and constipation; (6) past history of inflammatory bowel disease and celiac disease; (7) HbA1c level ≥ 9% at the time of consent; (8) use of alpha-glucosidase inhibitors within 4 weeks prior to consent; (9) cerebral infarction, stroke, or myocardial infarction within 12 weeks prior to consent; (10) severe hepatic dysfunction defined as alanine aminotransferase (ALT) or aspartate transaminase (AST) level 5 times equal or higher than the upper normal limit; (11) severe renal dysfunction defined as estimated glomerular filtration rate < 30 mL/min/1.73 m^2^; (12) active malignant tumor; (13) allergy history of bifidobacteria; (14) usage of any other supplements or medications that affect intestinal function; (15) usage of medications that are likely to cause abdominal symptoms (e.g., gastroprokinetic agents, drugs for dyspepsia, antiemetic agents, laxatives, and anticholinergics); (16) patients with changes in diet within 12 weeks prior to consent; (17) other conditions that the researcher or investigator thinks inappropriate for the study.

### Who will obtain informed consent?

Investigators or researchers will obtain written consent from the patients willing to participate in the trial. Patients will receive information sheets and discuss with investigators or researchers for the trial based on the information provided in the information sheets.

### Additional consent provisions for collection and use of participant data and biological specimens

If new information concerning this research is obtained, investigators and researchers will provide additional explanations to the participants and revise the consent document, as necessary.

### Interventions

#### Explanation for the choice of comparators

In this trial, no medication will be administered to the control group.

#### Intervention description

A flowchart for enrolment and follow-up visits is shown in Fig 1. Written informed consent and provisional registration will be obtained from all participants. Within 8 weeks of provisional registration, baseline examinations will be performed, and participants will be registered based on the aforementioned inclusion and exclusion criteria. Eligible patients will then be randomized into two groups (group A, BBG9-1 group; group B, control group) using the minimization method. Among the background factors of the study participants, age (<65 years or ≥65 years), sex, and the abdominal symptoms (constipation or diarrhea) are used as allocation factors. Patients assigned to group A will receive probiotic BBG9-1 oral administration (Biofermin® tablets containing 12 mg of bifidobacteria, 2 tablets 3 times a day) along with their current treatment for 12 (± 3) weeks, and patients assigned to group B will continue the current treatment for 12 (± 3) weeks without probiotic BBG9-1 oral administration. Subsequently, the examinations, which are the same as the baseline examinations, will be performed 12 (± 3) weeks after the baseline examinations. For patients assigned to group A, the date of initiation of medication will be the starting date of observation for the study. For patients assigned to group B, the date of sampling at the baseline examination will be the starting date of observation for the study. Research patients who are not enrolled in the study will be excluded from participation at the time of their failure to enroll. Such cases will not be counted as the target number of cases to be enrolled in the study.

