#### Outcomes

The primary endpoint of this trial will be the change in the total GSRS score from baseline to follow-up examination (12 ± 3 weeks after baseline examination). Secondary endpoints of this trial will be as follows: (1) change and percent change in following parameters from baseline to follow-up examination: GSRS subdomain scores, fecal properties/Bristol stool form scale, defecation frequency, blood test biomarkers (total bile acid, glycoalbumin, glucagon-like peptide-1, glucose-dependent insulinotropic polypeptide, glucagon, HbA1c, fasting plasma glucose, C-peptide, AST, ALT, gamma-glutamyltransferase, total cholesterol, high-density lipoprotein cholesterol, low-density lipoprotein cholesterol, triglycerides, blood urea nitrogen, and creatinine), physical examination (body weight and body mass index), urinary albumin creatinine ratio, gut microbiota (type of enterobacteria, relative abundance, alpha diversity, and beta diversity), macronutrients (total energy, carbohydrate, fat, protein, and dietary fiber intakes measured by brief-type self-administered diet history questionnaire [BDHQ]) [16]; (2) proportion of participants whose fecal property of Bristol stool form scale is within normal range (3.5–4.5); (3) medication adherence to the BBG9-1; (4) factors that affect GSRS total score or constipation/diarrhea subdomain scores; (5) stratification of following items by baseline symptoms (constipation/diarrhea): GSRS total score, GSRS subdomain scores, proportion of participants whose fecal properties are within normal range, defecation frequency, blood test biomarkers, and gut microbiota. The exploratory endpoints of this trial will be as follows: (1) blood, urine, and stool metabolomes (short, medium, and long chain fatty acids, amino acids, carbohydrates, and bile acids); (2) items other than nutrients evaluated in the secondary endpoints and items evaluated by the diabetes treatment satisfaction questionnaire (DTSQ) [17]; (3) items other than physical examination evaluated in the secondary endpoints; (4) items other than gut microbiota evaluated in the secondary endpoints; (5) change in lipopolysaccharide-binding protein; (6) subgroup analysis by age, sex, etc. Harm outcomes will also be evaluated based on various laboratory abnormalities and adverse reactions to the medication.

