**Fig 2 pone.0295998.g002:**
[figure not shown]
Schedule of enrolment, interventions, and assessments. *, Must be performed prior to initiation of the *Bifidobacterium bifidum* G9-1. ALT, alanine aminotransferase; AST, aspartate transaminase; BBG9-1, *Bifidobacterium bifidum* G9-1; GSRS, Gastrointestinal Symptom Rating Scale.

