#### Reporting of adverse events and harms

The incidence of diseases and adverse events will be used as a safety measure. These events will be recorded using CRF throughout the observation period. The analysis will be conducted using a safety analysis population after data fixation. Any unfavorable medical event that occurs to a research participant during the course of this study, including an exacerbation of previous illnesses, will be treated as an “adverse event.” Worsening of diabetes-related macrovascular and microvascular complications at the time of initiation of medication will also be treated as an adverse event. In this study, if the data related outcomes, including primary endpoints, secondary endpoints and exploratory endpoints, worsens, it will not be treated as an adverse event. When an adverse event will be observed, researchers will immediately take appropriate measures and report necessary information. If administration of BBG9-1 is discontinued or treatment for an adverse event becomes necessary, the researchers will inform the research participant.

If an adverse event occurs, the name, timing, degree, severity, outcome, date of confirmation of the outcome, relevance to the study, reason for judgment, suspect medication(s), treatment of the suspect medication(s), and other treatment details shall be recorded in the CRF. In principle, symptoms observed during the study will be followed-up until they normalize or recover to a level not considered an adverse event, or until symptoms stabilize or will be fixed in the case of irreversible adverse events due to organic damage.

The degree of adverse events will be classified according to the following criteria: mild, not detrimental to daily life; moderate, interference with daily life but only to the extent that activities can be performed with considerable patience; severe, to the extent that it significantly interferes with the performance of daily activities.

The outcome of adverse events will be classified according to the following criteria: recovery, recovery to a level that is normalized or not considered an adverse event; slightly relieved, symptoms have lessened but have not normalized; unrecovered, symptoms have not yet normalized at the time of the event; recovered but with residual aftereffects, recovered but still dysfunctional to the extent that it interferes with daily life; death; unknown, the outcome is unknown due to interruption of hospital visits.

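### Observation starts at first dose in group A but at pre-randomisation baseline sampling in group B, so adverse-event and logbook windows can differ by arm

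*Protocol article*

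**What the plan says.** Under Intervention description, the protocol article sets the start of observation separately for each arm:

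- Group A: "For patients assigned to group A, the date of initiation of medication will be the starting date of observation for the study".
- Group B: "For patients assigned to group B, the date of sampling at the baseline examination will be the starting date of observation for the study".

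The same section places randomisation after the baseline examinations: "Eligible patients will then be randomized into two groups (group A, BBG9-1 group; group B, control group) using the minimization method". The Methods part of the abstract agrees, with assignment made "after the baseline examination". The Fig 2 legend marks certain items with "Must be performed prior to initiation of the" study product. That fixes their order but neither states nor limits the time between them.

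Reporting of adverse events and harms ties safety data to this clock: "These events will be recorded using CRF throughout the observation period". Plans for assessment and collection of outcomes does the same for the logbooks of defecation frequency, stool form and adherence. The statistical methods section plans a listing of adverse events by group with Fisher's test if needed, and states no adjustment for time observed.

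The follow-up examination has one anchor in both arms. It "will be performed 12 (± 3) weeks after the baseline examinations", and Outcomes defines the primary endpoint over that same interval.

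**The concern.** In a randomised comparison of harms, each arm should be at risk of having an event counted for the same length of time, beginning at or after allocation. Here group B's clock starts before allocation and group A's starts after it, at first dose. An event between baseline sampling and the date on which a group A patient would start tablets lies inside the window in group B and outside it in group A.

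The effect runs one way. Any gap lengthens the control window and so tends to raise the control arm's count. Because the planned comparison is of simple proportions, nothing in the stated analysis would correct for this. Events in group A that were never recorded could not be recovered at analysis. The logbook data, which feed several secondary endpoints, run on the same unequal clock.

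**Working it through.** **The plan's own figure.** The only computed figure in the article is the sample size: 2 × (1.960 + 0.842)² × 0.412² / 0.244² = 44.8, so 45 per group, and 45 / 0.90 = 50 per group. It reproduces and does not depend on the point made here.

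**Inputs.**
- Start of observation: first dose in A, baseline sampling in B (Intervention description).
- Common end: the follow-up examination, v weeks after baseline, where v is 12 with a permitted range of 9 to 15 (Intervention description; Outcomes).
- L, the weeks from baseline sampling to first dose in A: not stated. It is assumed here to be 0 to 4.

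**Window lengths.** Group B is observed for v weeks and group A for v − L. The shortfall in A is L / v.

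| L (assumed) | A, v = 12 | B, v = 12 | B / A | Shortfall, v = 12 | Shortfall, v = 9 | Shortfall, v = 15 |
|---|---|---|---|---|---|---|
| 0 | 12 | 12 | 1.00 | 0% | 0% | 0% |
| 1 | 11 | 12 | 1.09 | 8.3% | 11.1% | 6.7% |
| 2 | 10 | 12 | 1.20 | 16.7% | 22.2% | 13.3% |
| 4 | 8 | 12 | 1.50 | 33.3% | 44.4% | 26.7% |

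**What this does to crude proportions.** Suppose the product has no effect on events and the hazard is constant and equal in both arms. Let p be the chance of at least one event in 12 weeks; the article gives no value. Group A would then show 1 − (1 − p)^((12 − L)/12).

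| p (assumed; shown by B) | A, L = 1 | A, L = 2 | A, L = 4 |
|---|---|---|---|
| 10% | 9.2% | 8.4% | 6.8% |
| 20% | 18.5% | 17.0% | 13.8% |
| 30% | 27.9% | 25.7% | 21.2% |

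With 50 per group and p = 20%, group B would have 50 × 0.20 = 10 patients with an event. Group A would have 50 × 0.185 = 9.25, 50 × 0.170 = 8.5 and 50 × 0.138 = 6.9. The date rule alone would produce a difference of about 1 to 3 patients.

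**Primary endpoint interval.** It runs from the baseline examination to v weeks after it in both arms. L does not enter.

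**Treatment period and examination in group A.** If treatment runs from first dose to the examination, it lasts v − L weeks. At v = 12 this is 11 or 10 weeks for L of 1 or 2, inside the stated 12 ± 3. For L = 4 it is 8 weeks, below the lower limit of 9. Both tolerances could then be met only with an examination at week 9 + 4 = 13 or later.

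**The case against.** The strongest reply is that the gap may be trivial. Allocation is made through a web system and could take place on the day of the baseline examination or within days, and nothing in the article supports a gap of 4 weeks. If tablets start on the day of sampling, the two clocks coincide. This stands, and it limits the size of the point. It does not remove it, because the article neither requires a same-day start nor caps the interval.

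It can also be said that starting group A at first dose captures all exposed time, and that events before dosing cannot be effects of the product. That is true of group A alone, but a fair comparison needs an equivalent window in group B, and the rule does not give one. The harms section also defines an adverse event broadly, as anything untoward arising in the course of the study, so sites might record group A events before first dose anyway. That is possible, but the sentence on recording points the other way. The choice should not rest with sites. Finally, harms are not the primary endpoint and the test is optional, so the consequence is modest.

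A reader might go further and infer an efficacy bias: that group A has longer from baseline to follow-up, and so more time for the untreated improvement of 0.197 used in the sample size section. The documents do not support this. Intervention description and Outcomes time the examination from baseline in both arms, and the data collection section times the week-12 survey forms the same way. The sample size section gives no duration for the untreated period, so a drift per week cannot be derived from it. Under the schedule as written, a gap would shorten group A's exposure before the endpoint, which if anything works against BBG9-1.

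A reader might also call the treatment period and the examination timing flatly contradictory. They are not: the ± 3-week tolerances accommodate a gap of 1 or 2 weeks when the examination falls at week 12. They merely cannot both fall at exactly 12 weeks when there is a gap.

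**Conclusion.** The point holds for the observation period and for what is collected over it, namely adverse events and logbook data. The unequal start is the article's own rule, not a detail left to a fuller document. With a common end visit, group B's window exceeds group A's by L weeks and includes time before allocation. The excess is 0 weeks if dosing starts on the day of sampling, and for assumed gaps of 1, 2 and 4 weeks it gives 11, 10 and 8 weeks in A against 12 in B. Crude event proportions could then modestly favour BBG9-1. The true size cannot be fixed from the document, since both the gap and the event rate are assumptions.

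The point does not extend to the primary endpoint, whose interval is the same in both arms, or to the sample size.

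**What to change.** - In Intervention description, give both arms one start of observation: the date of randomisation. Allocation runs through the web system, so this date should already be held there.
- Count adverse events and logbook data from that date in both arms, and align Reporting of adverse events and harms with it. The baseline examination keeps its role as baseline.
- Report, by arm, the interval from baseline examination to randomisation and, for group A, the interval from randomisation to first dose.
- Leave the visit timing in Outcomes unchanged, since its anchor is already common to both arms.
- Within Intervention description, reconcile the treatment period in group A with an examination timed from baseline, so that sites do not resolve it differently. How that is done is for the investigators.

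The cost is a change of protocol wording and one date rule in the data system. No sample size figure changes. If recruitment is under way, events in group A between randomisation and first dose need to be collected from the change onward, and any earlier gap in recording should be stated in the report.

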**Fig 1 pone.0295998.g001:**
[figure not shown]
Study design of Binary STAR study.

#### Criteria for discontinuing or modifying allocated interventions

The criteria for discontinuation of observation are as follows: (1) failure to register; (2) worse glycemic control (HbA1c ≥ 10%); (3) withdrawal of consent; (4) serious incompatibility after registration; (5) discontinuation of medications because of worsening of disease and/or complications; (6) discontinuation of the trial because of illness or adverse events; (7) pregnancy; (8) significant nonadherence (< 75% of the number of tablets each participant plans to take internally or > 120%); (9) significant deviation from the research protocol; (10) investigator/researcher’s determination to stop the study for other reasons. The data shall be fixed by the Data Handling Committee after handling in a blinded manner. Even if there is a deviation from the research protocol, observations shall be continued as much as possible.

The criteria for discontinuation of the trial are as follows: (1) significant information regarding the quality, safety, or efficacy of Biofermin® tablets is obtained; (2) recruitment of research participants is difficult, and there is a large discrepancy from the planned number of cases; (3) the objective of the research is achieved before the planned number of cases or planned duration is reached; (4) instructions to change the research plan, and it is difficult to accept these instructions.

